### Review of primary outcome

During the early part of the trial, and with advice from the DMC, the primary outcome definition was refined to ensure it captured babies who were likely to have experienced hypoxia during labour. The component of the primary outcome “*Admission to neonatal unit within 48 h of birth for ≥ 48 h with evidence of feeding difficulties, respiratory illness or encephalopathy (where there is evidence of compromise at birth)*” was initially capturing a range of conditions, many of which were unlikely to be related to hypoxia. As a consequence, a process of reviewing each case which fulfilled this component of the primary outcome was implemented. Neonatal unit discharge summaries are collected for all babies admitted to the neonatal unit within 48 h of birth for more than 48 h. For the purposes of data monitoring during the trial, two members of the co-investigator group reviewed all cases which fulfilled this criteria and using a defined data extraction form, ascribed each case as meeting the primary outcome or not. The data extraction form included key elements of the neonatal course which are most likely to be related to intrapartum hypoxia. The form is not an established or validated list of criteria and the numeric scoring was devised to give some quantification of the severity of elements of the clinical course. A score of 3 or greater was agreed to be evidence that the condition of the baby was likely to be associated with intrapartum hypoxia, acknowledging that there remained uncertainty about this, as there is no absolute measure of intrapartum hypoxia. For the final analysis, all cases meeting the broad primary outcome criteria will be reviewed by an independent panel of neonatologists to repeat this process of ascribing each case (masked to allocation) as fulfilling the definition fo the primary outcome or not. Each case will be reviewed (independently) by at least 2 neonatologists and disagreements will be resolved by discussion by the group of five neonatologists.

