**Methods and design:**

An individually randomised controlled trial of 46,000 women who are judged to require continuous electronic fetal monitoring in labour.

*Eligibility criteria:* Women admitted to a participating labour ward who are judged to require continuous electronic fetal monitoring, have a singleton or twin pregnancy, are ≥ 35 weeks’ gestation, have no known gross fetal abnormality and are ≥ 16 years of age.

*Exclusion criteria:* Triplets or higher order pregnancy, elective caesarean section prior to the onset of labour, planned admission to NICU.

*Trial interventions:* Computerised interpretation of the CTG with decision-support.

Primary outcomes: *Short term:* A composite of ‘poor neonatal outcome’ including stillbirth after trial entry, early neonatal death except deaths due to congenital anomalies, significant morbidity: neonatal encephalopathy, admissions to the neonatal unit with 48 h for > 48 h with evidence of feeding difficulties, respiratory illness or encephalopathy where there is evidence of compromise at birth. *Long term:* Developmental assessment at the age of 2 years in a subset of 7000 surviving babies.

*Data Collection:* For all participating women and babies, labour variables and outcomes will be stored automatically and contemporaneously onto the Guardian® system.

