#### Short term

A composite of ‘poor neonatal outcome’ to include (a) all deaths *(intrapartum stillbirths plus neonatal deaths* i.e. *deaths up to 28 days after birth)* except deaths due to congenital anomalies, (b) significant morbidity: neonatal encephalopathy (moderate and severe); (c) admissions to the neonatal unit within 48 h of birth for ≥ 48 h with evidence of feeding difficulties, respiratory illness or encephalopathy where there is evidence of compromise at birth. (We recognise that the signs of mild encephalopathy can be subtle and hence a number of such babies are likely to have a range of non-specific signs such as respiratory difficulty and poor feeding rather than features more specifically associated with encephalopathy [27]. Hence including admission to the neonatal unit within 48 h of birth for equal to or greater than 48 h where there is evidence of compromise at birth. Since this is a mature group of babies, any difference in the incidence of these admissions is likely to result from differences in perinatal asphyxia).

*Note: the benefit of using a composite outcome is the increased incidence of the outcome; hence the sample size is reduced. The main problem occurs if the intervention affects different outcomes in different ways. In this trial, if the use of the decision-support software decreased deaths but increased significant morbidity there may be no difference in the short term primary outcome between the two arms of the trial, even though deaths were being prevented in one arm. The probability of this situation occurring appears very small. If decision-support prevents perinatal asphyxia it will have an effect on all the outcomes contained within the combined primary outcome.*

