#### Data monitoring committee

An independent Data Monitoring Committee (DMC) has been established for the trial. This is independent of the trial organisers and will meet yearly. The terms of reference for the DMC were agreed at their first meeting. A DMC charter has been completed following the recommendations of the DAMOCLES Study [43].

During the period of recruitment to the trial, interim analyses will be supplied, in strict confidence, to the DMC, together with any other analyses the DMC may request. The data will be supplied to the Chair of the DMC as frequently as they request. Meetings of the committee will be arranged periodically, as considered appropriate by the Chair. In the light of interim data, and other evidence from relevant studies (including updated overviews of the relevant randomised controlled trials), the DMC will inform the TSC, if in their view there is proof beyond reasonable doubt that the data indicate that any part of the protocol under investigation is either clearly indicated or contra-indicated, either for all women or for a particular subgroup of trial participants. A decision to inform the TSC will in part be based on statistical considerations. Appropriate criteria for proof beyond reasonable doubt cannot be specified precisely. A difference of at least 3 standard errors in the interim analysis of a major endpoint may be needed to justify halting, or modifying, such a study prematurely. If this criterion were to be adopted by the DMC, it would have the practical advantage that the exact number of interim analyses would be of little importance, and so no fixed schedule is proposed [44]. Unless modification or cessation of the protocol is recommended by the DMC, the TSC, collaborators and administrative staff (except those who supply the confidential information) will remain blind to the results of the interim analysis. Collaborators and all others associated with the study may write through the trial office to the DMC, to draw attention to any concern they may have about the possibility of harm arising from the treatment under study, or about any other matters that may be relevant.

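### The primary composite and the eligibility rules are stated inconsistently, and the mid-trial refinement of the admission component is not carried through the text or fully explained

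*Protocol article*

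**What the plan says.** **Abstract, Methods and design.** The composite is described as "including stillbirth after trial entry, early neonatal death except deaths due to congenital anomalies", followed by "significant morbidity: neonatal encephalopathy, admissions to the neonatal unit with 48 h for > 48 h" with further conditions. Encephalopathy has no grade here. The exclusions include "planned admission to NICU".

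**Outcome measures, Short term.** Deaths are intrapartum stillbirths plus neonatal deaths, the latter defined as "deaths up to 28 days after birth". Encephalopathy as a component in its own right must be moderate or severe. The admission component, (c), needs a stay of 48 h or longer. No panel acceptance and no score are mentioned. Secondary outcomes repeats component (c) in the same broad wording.

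**Trial eligibility and randomization; Exclusion criteria.** Neither list mentions planned NICU admission.

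**Review of primary outcome.** The text reports: "During the early part of the trial, and with advice from the DMC, the primary outcome definition was refined". The reason given is that component (c) was picking up many conditions unlikely to be related to hypoxia. Cases are now reviewed on a data extraction form that the article itself describes as neither established nor validated. On the cut-off it says: "A score of 3 or greater was agreed to be evidence that the condition of the baby was likely to be associated with intrapartum hypoxia". For the final analysis an independent panel of neonatologists, masked to allocation, repeats the process. Discharge summaries are collected for stays of more than 48 h.

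**Data monitoring committee.** During recruitment "interim analyses will be supplied, in strict confidence, to the DMC". A difference of 3 standard errors on a major endpoint is offered as a possible guide for stopping.

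**The concern.** The primary event set and the eligible population depend on which part of the article is followed. The effect spreads, because having the trial primary outcome also selects children for the 2-year follow-up, cases for the quality-of-care review and infants for the economic sample.

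The most consequential difference is in component (c). The review section narrows it to accepted cases, but the two outcome lists were not updated. A reader of the outcome lists alone would expect the broad component in the primary result.

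The change was made during the trial, on advice from a committee that is sent interim analyses. When an endpoint is changed mid-trial, readers need to know what was known by arm at the time and what the result looks like under the unrefined definition. The article gives neither.

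**Working it through.** **1. The texts side by side**

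| Element | Abstract | Outcome and eligibility sections | Review of primary outcome |
|---|---|---|---|
| Stillbirth | after trial entry | intrapartum | not restated |
| Neonatal death | early | to 28 days | not restated |
| Encephalopathy as its own component | no grade | moderate or severe | not restated |
| Neonatal-unit stay | more than 48 h | 48 h or longer | criterion 48 h or longer; summaries collected for more than 48 h |
| Acceptance of admission cases | none | none | masked panel, using the scored form |
| Planned NICU admission | excluded | not excluded | not addressed |

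The stillbirth wordings differ little in practice, because women are randomised in labour. The other rows can change who is counted or who is eligible. Within the review section, a stay of exactly 48 h meets the criterion but has no discharge summary to review. Few babies should be affected, but the number depends on how length of stay is recorded, which the article does not say.

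**2. The plan's own sample size**

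Inputs from Effect size: p1 = 0.003, p2 = 0.0015, 5% level, 90% power, 23,000 per arm. Sidedness is not stated there; two-sided is assumed.

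n per arm = [z(0.975)·√(2·p̄·(1 − p̄)) + z(0.90)·√(p1(1 − p1) + p2(1 − p2))]² / (p1 − p2)², with p̄ = 0.00225.

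This gives 20,966 per arm, 41,932 in total. With continuity correction the total is 44,558. Power at 23,000 per arm is 92.4% uncorrected, 90.9% continuity-corrected and 91.6% by Fisher's exact test. The stated 90% therefore reproduces, and 46,000 is a slightly conservative rounding.

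**3. How much of the composite is component (c)?**

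From the incidence sections: 0.35 + 0.7 + 1.3 = 2.35 per 1000 for deaths and moderate or severe encephalopathy. The planned total is 3 per 1000, so 3 − 2.35 = 0.65 per 1000 is left for admissions: 0.65 / 3 = 22%. In a control arm of 23,000 that is about 15 of 69 expected events. The article calls 3 per 1000 cautious; with mild encephalopathy added in full (1.25) the total would be 3.6.

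**4. What the broad wording could do to the estimate**

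Assume 3 per 1000 hypoxia-related cases with risk ratio 0.50, plus u unrelated admissions per 1000 with risk ratio 1. The overall risk ratio is (1.5 + u) / (3 + u). The values of u are assumptions; the article gives none. Power is for 23,000 per arm, two-sided 5%, uncorrected.

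| u per 1000 | Overall risk ratio | Power |
|---|---|---|
| 0 | 0.50 | 92% |
| 1 | 0.63 | 81% |
| 2 | 0.70 | 70% |
| 3 | 0.75 | 61% |
| 6 | 0.83 | 43% |

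**5. Early against 28-day death**

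0.7 per 1000 × 23,000 = 16 expected neonatal deaths in the control arm. If 10% to 30% of them fall after the early period (assumed), the choice moves 2 to 5 of 69 control events.

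**The case against.** The case on the other side has real weight.

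- The abstract is the outlier on deaths. The body agrees with itself on 28 days, and on 48 h or longer as the criterion. An attentive reader can assemble the intended definition, and the review section does separate the broad criteria from final acceptance.
- The refinement has a stated clinical reason that could be seen in pooled data. It is placed early in the trial, and the review process is recorded in Table 3. The form's limits are admitted openly.
- Final classification is by an independent masked panel, with at least two reviewers per case. The Data monitoring committee section keeps the TSC, collaborators and most administrative staff blind to interim results.
- Data collection provides for extraction from the notes of all admitted babies, so a 48 h stay is not without information, only without a summary.

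Three stronger readings are tempting, and the article does not support them.

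- A reader might infer that the endpoint was chosen on results by arm. Nothing says the DMC had seen such results when it advised. The article is silent either way.
- A reader might infer that no analysis under the unrefined definition is planned. The article states none for the composite, but the SAP is not shown and could contain one. The broad admission component also remains a secondary outcome, although it is unclear whether it is counted before or after review.
- A reader might remove component (c) altogether and report power falling from 92.4% (3 per 1000) to 85.2% (2.35 per 1000). The arithmetic is right, but no part of the article removes the component, so the figure describes none of the competing definitions.

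What stands after this is the inconsistency of the texts and the missing statement of what was known. Masked review protects the classification of individual cases. It does not show how the rule itself came to be chosen.

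**Conclusion.** The point holds as one of inconsistent definition and incomplete disclosure, and it should be settled before the final analysis because it concerns the primary endpoint. It is not evidence that the refinement was driven by results.

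The early/28-day choice is small: 2 to 5 of 69 control events under an assumed 10% to 30%. The broad/accepted choice for component (c) can be large. The planning rates give the component 22% of events, and the dilution illustration moves a risk ratio of 0.50 to between 0.63 and 0.83. That range rests on assumed rates of unrelated admissions and on no effect of the intervention on them. It also supports the sponsor's reason for narrowing the component. The case is for stating the accepted version everywhere and showing the other beside it, not for reversing the change.

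**What to change.** 1. Use one definition in the abstract, Short term, Secondary outcomes and Review of primary outcome: the outcomes-section wording (intrapartum stillbirth and death to 28 days, moderate or severe encephalopathy, stay of 48 h or longer), with component (c) as accepted by the masked panel. Say whether the secondary outcome is counted before or after review.
2. Collect discharge summaries for stays of 48 h or longer, to match the criterion.
3. Reconcile planned NICU admission between the abstract and the two eligibility lists. Which rule applies is for the sponsor to state.
4. State what the DMC and the investigators knew, by arm or pooled, when the definition was refined.
5. Report the composite with the unrefined component (c) as a sensitivity analysis using the same primary model, or point to the SAP if it is already there.

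The cost is text edits, summaries for any stays of exactly 48 h, and one extra model run; the cases meeting the broad criteria are already collected for review. The drawback is that the unrefined estimate is likely to be diluted towards 1, so it should be read as context for the primary result and not as a second test.

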#### Effect size

The effect size which can be detected with 46,000 women (23,000 in each group), assuming a 5 % level of significance and 90 % power, is a 50 % reduction in poor neonatal outcome rate from 3 to 1.5 per 1000. We have approximated the number of women recruited with the number of infants born, even though women with a twin pregnancy are eligible to join the trial. Approximately 1 in 80 pregnancies are twin pregnancies, however, a proportion of these births will occur before 35 weeks’ gestation and a large proportion of the term births will be by elective caesarean section. We therefore estimate that fewer than 1 % of all births in the study will be twins. In a study of 164 preterm infants [29], the mean (SD) PARCA-R composite score at 2 years was 80 (SD 33) and the mean Mental Development Index (Bayley Scales of Infant Development II) was approximately half a standard deviation below the standardised mean of 100. If we assume that a normal group of term infants would have a PARCA-R composite score half a standard deviation above this sample of preterm infants, then we can estimate a mean (SD) 2 year score of 96 (SD33). Based on this estimate, a follow up sample of size 7000 (3500 per arm) in the INFANT study would have over 90 % power to detect a difference of 3 points in the PARCA-R component score with a two-sided 5 % significance level. The incidence of severe metabolic acidosis (cord-artery pH <7.05) is 10 per 1000 [36–39]. Our proposed sample size will therefore enable us to detect a 28 % relative risk reduction in incidence with over 80 % power in those babies who have their cord artery pH measured.

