#### Data collection

For all participating women and babies, labour variables and outcomes will be stored automatically and contemporaneously onto the Guardian® system. Data collected via the system will be sent electronically to the trial co-ordinating centre at the UCL Clincial Trials Unit (UCL CTU) in London. Data will be extracted from the notes of babies admitted to the neonatal unit and for all neonatal deaths. It should be noted that not all data fields are collected at every centre. However, where an item is collected these data will be sent to the UCL CTU. The trial is not collecting the reason why continuous EFM is being used, as this is not recorded. All children surviving to be discharged home from hospital following their birth will be ‘flagged’ at the NHS Information Centre for those born in England and Scotland and all deaths occurring after discharge home from hospital will be notified to the trial co-ordinating centre at the UCL CTU. At 2 years after trial entry a sample of 7000 surviving children (3500 in each group) will be followed up at 2 years of age. This sample will be taken from within the sample recruited during the first 2 years of the project so that follow-up of this group can be completed around the time that the trial stops recruiting. As there seems little possibility that the nature of the effect of the intervention will vary over the duration of trial recruitment, this process will be the most efficient use of resources. For children in the follow-up group, their family will be sent a two part parent-completed questionnaire to assess the child’s health, development and well-being. The first part of the questionnaire comprises the PARCA-R, which has been previously validated as a means of assessing neurodevelopment in a trial setting. The second part focuses on general health issues, and has also been used previously [28, 29]. Major disability at 2 years will be assessed by questionnaires sent to the child’s parents and health care professionals. Major disability will be defined according to the criteria set out in the National Perinatal Epidemiology Unit (NPEU) and Oxford Regional Health Authority document and will include any major disability in the following domains: neuromotor function, seizures, auditory function, communication, visual function, cognitive function and other physical disability [30, 31].

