#### Primary analysis

The primary analysis will be a comparison of women and babies allocated to “CTG with no decision support” with “CTG with decision support”. Participants will be analysed in the groups into which they were randomly allocated, regardless of allocation received. All women and babies with available data will be included, except for protocol violations and women randomised in error who did not give consent or who were under 16 years of age. The number (percentage) of babies with the composite primary outcome will be presented for each group, and the risk ratio plus 95 % confidence interval (CI) will be calculated. Risk ratios will be estimated using generalised estimating equations (GEE), or a similar method, adjusting for the stratification factors used in the randomisation (centre and singleton/twin pregnancy). This method of analysis will account for the correlation in outcomes between twins and siblings delivered in a subsequent pregnancy during the trial period. A log binomial model will be used in the first instance, but if convergence is not achieved then a log Poisson model will be used with a robust variance estimator [40]. The mean (SD) PARCA-R Composite score will be presented for each group, and the mean difference between groups plus 95 % CI will be calculated and compared using GEE (Gaussian model with identity link). For secondary outcomes including the components of the primary outcome, a 1 % level of statistical significance will be employed. Both adjusted and unadjusted estimates will be presented for all outcomes, but the primary inference will be based on the adjusted analysis.

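### The stated power of over 80% for a 28% reduction in metabolic acidosis holds at 5%, but this is a secondary outcome tested at 1%, where power is about 75% at best

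*Protocol article*

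**What the plan says.** All references are to the protocol article.

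- **Effect size, incidence.** "The incidence of severe metabolic acidosis (cord-artery pH <7.05) is 10 per 1000".
- **Effect size, power.** The proposed sample is said to be able to "detect a 28 % relative risk reduction in incidence with over 80 % power in those babies who have their cord artery pH measured". The sentence names no significance level, no sidedness and no share of babies measured.
- **Effect size, the other two power statements.** Both use 5%. For the composite: "The effect size which can be detected with 46,000 women (23,000 in each group), assuming a 5 % level of significance and 90 % power". For the two-year score: "over 90 % power to detect a difference of 3 points in the PARCA-R component score with a two-sided 5 % significance level".
- **Secondary outcomes.** Metabolic acidosis is in this list, defined by cord artery pH below 7.05 together with a base deficit of at least 12 mmol/l.
- **Primary analysis.** "For secondary outcomes including the components of the primary outcome, a 1 % level of statistical significance will be employed". No section exempts acidosis.
- **Data collection.** "It should be noted that not all data fields are collected at every centre".

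**The concern.** The acidosis power sentence sits beside two calculations made at 5% and appears to have been made at the same level. The analysis section then holds the outcome to 1%. If so, the article states a power that its own testing rule does not deliver.

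Two further features push the same way. The claim is limited to babies with a measured pH, but no share is given. The incidence used is for a looser definition than the outcome to be analysed.

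What is at stake is interpretation. This is the only secondary outcome for which the article states a power. A non-significant result at 1% would be read as coming from a test with over 80% power for a 28% reduction.

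**Working it through.** **Inputs**

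- n = 23,000 per arm, 1:1, counting women as infants (Effect size).
- p1 = 0.0100 (Effect size). p2 = 0.72 × 0.0100 = 0.0072, so d = 0.0028.
- α = 0.05 as in the neighbouring calculations, or 0.01 under the Primary analysis rule.
- Two-sided: stated for the two-year score and assumed here. The article plans no one-sided test.
- Share measured: not given. 100% is the best case; 80% is an assumption for illustration.

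**Formulas** (two-proportion normal approximation, pooled variance under the null)

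- p̄ = (0.0100 + 0.0072)/2 = 0.0086
- S0 = √[2p̄(1 − p̄)] = √0.017052 = 0.13058
- S1 = √[p1(1 − p1) + p2(1 − p2)] = √0.017048 = 0.13057
- Power = Φ{[d − z(1−α/2) × S0/√n] / (S1/√n)}
- n per arm for 80% power = [z(1−α/2) × S0 + 0.8416 × S1]² / d²

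**Step 1. Reproduce the stated figure at two-sided 5%.** With n = 23,000, S0/√n = 0.00086104 and S1/√n = 0.00086094.

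- Power = Φ[(0.0028 − 1.9600 × 0.00086104)/0.00086094] = Φ(1.292) = 90.2%.
- n for 80% = (1.9600 × 0.13058 + 0.8416 × 0.13057)²/0.0028² ≈ 17,070 per arm, and 17,070/23,000 = 74%.

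The stated figure therefore reproduces at 5% once about three quarters of babies are measured.

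**Step 2. Apply the 1% level.**

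- Power = Φ[(0.0028 − 2.5758 × 0.00086104)/0.00086094] = Φ(0.676) = 75.1%.
- n for 80% = (2.5758 × 0.13058 + 0.8416 × 0.13057)²/0.0028² ≈ 25,400 per arm, and 25,400/23,000 = 110%.

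**Step 3. Vary the share measured.**

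| Share measured | Babies per arm | Power at 5% | Power at 1% |
|---|---|---|---|
| 100% | 23,000 | 90.2% | 75.1% |
| 90% | 20,700 | 87.0% | 69.5% |
| 80% | 18,400 | 82.9% | 63.0% |
| 75% | 17,250 | 80.4% | 59.5% |

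No share of up to 100% gives 80% at two-sided 1%.

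**Step 4. Check that the method does not drive the answer.** At two-sided 1% with every baby measured, a continuity correction gives 73.4% and a Wald test on the log risk ratio gives 74.6%. Adding 1% more babies for twins ("We therefore estimate that fewer than 1 % of all births in the study will be twins") gives 75.6%.

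**Step 5. Find the detectable reduction at 1% with 80% power, from 10 per 1000.** Solving the power formula for p2 gives about 29.3% with all babies measured and about 32.5% with 80% measured.

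**Step 6. Compare the definitions.** The 10 per 1000 is attached to pH below 7.05. The listed outcome requires that and a base deficit of at least 12 mmol/l, so its incidence can equal but not exceed the incidence of pH below 7.05 alone. For the same relative reduction, power is then the same or lower. The article does not say by how much.

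**The case against.** **The figure is not miscalculated.** At 5%, the level used beside it, it is right, and the gap between 90% and the stated 80% leaves room for incomplete sampling. This stands. The defect is an unstated level that disagrees with the testing rule elsewhere in the article.

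**Incomplete sampling is disclosed.** The sentence is limited to babies with a measured pH. This also stands; only the assumed percentage is missing. The powers below full coverage rest on shares chosen here. The 75% does not, because it is the best case.

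**A one-sided 1% test would rescue the claim.** It gives 82.3% at full coverage, but the article plans no such test.

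**The incidence could be higher.** The article argues that women selected for continuous monitoring may be at higher risk, but it says so of deaths and encephalopathy, not of acidosis. About 11 per 1000 would be needed for 80% power at 1% with every baby measured. The sentence states 10.

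**It is one secondary outcome among many.** This is correct. The sample size rests on the composite, and in the best case the gap is about 5 points of power, or 29.3% against 28% in detectable reduction.

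A reader might infer three stronger points that the article does not support:

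- **A known, larger loss of power from the stricter definition.** Any specific incidence below 10 per 1000 would be an assumption, so only the direction is established.
- **Bias from restricting the comparison to sampled babies.** Clinicians are unmasked, which makes arm-dependent sampling possible, but nothing says that sampling depends on allocation.
- **Acidosis as the leading objective marker of intrapartum hypoxia.** The Secondary outcomes section does not rank it so.

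**Conclusion.** The concern holds as an internal inconsistency. Under the article's own 1% rule, the design does not have over 80% power for a 28% reduction from 10 per 1000. It has about 75% if every baby is measured, and about 63% if 80% are. The conclusion assumes a two-sided test and the stated 23,000 per arm, and the alternative two-sided methods tried give 73% to 76% at full coverage. The definition mismatch can only leave power unchanged or reduce it.

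It would be wrong to infer that the trial is too small or that its primary calculation is affected. Neither the primary sample size nor the primary analysis depends on this sentence. Severity is minor to moderate.

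**What to change.** Restate the power sentence in the Effect size section so that it gives:

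- the two-sided 1% level;
- the outcome as defined under Secondary outcomes (pH and base deficit together);
- the incidence assumed for that outcome, with its source;
- the assumed share of babies with a cord gas.

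If 10 per 1000 can be justified for the full definition, suitable wording would be: at a two-sided 1% level, the design has 80% power for a reduction of about 29.3% if all babies are measured, or about 32.5% (say 33%) if 80% are measured. If the incidence is lower, the detectable reduction must be recalculated and will be larger.

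The cost is one reworded and less favourable sentence. Enrolment, the primary analysis and the 1% rule stay as they are.
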